### Modelling for primary tooth lifetime horizon

We will construct a decision analytic modelling framework to extrapolate the findings considering a longer time horizon (the primary molar lifetime) (Supplemental File 3). As the base case, we will consider a child as those enrolled in the trial. Then, based on the mean age of children enrolled on the main trial, we will establish the number of cycles of the Markov model.

Probabilities and costs will be extracted from the main trial. If necessary, any additional reference value will be identified from the literature. The SG experiment will generate utility values. We will assume that probabilities will maintain the same at each cycle during the time horizon. The half-cycle correction will be used to account for the fact that events and transitions can occur at any point during the cycle, not necessarily at the start or end of each cycle.

We will adopt the same strategies adopted in the trial-based analyses for deterministic and probabilistic analyses using the model framework. The final interpretation of uncertainties will be considered for this longer time horizon. Data will be modelled and analyzed using a Markov simulation model. Tree Age Pro 2017 (TreeAge Software, Williamstown, MA, USA).

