To date, there is no consensus on the best strategy to adopt in clinical practice, and most studies do not explore the clinical relevance of the accuracy tests nor patient-centered outcomes [2]. An ongoing clinical trial (CARies DEtection in Children - CARDEC-03) aims to assess the impact of using the FDI and CARS criteria in the assessment of restorations in primary teeth [7]. At first glance, when using a more interventionist strategy (using the FDI criteria), the indication of replacements of restorations in the baseline was more frequent than using the strategy based on CARS [8]. Nevertheless, the resources related to the long-term health effects have not been explored yet.

When defective restorations in primary teeth need to be assessed to guide their management, it is not known if this minimally invasive strategy is efficient for allocating resources compared to the conventional strategy, based on FDI criteria. Even if the diagnostic method benefits patients, the subsequent financial impact should be assessed, featuring phase 5 studies for diagnostic methods [9]. As dental expenditure was $298 billion in 2010, representing 4.6% of global healthcare costs [10], economic evaluations to direct resources to the best diagnostic strategies are critical for clinical practice to be financially viable. On the other hand, economic evaluations assessing diagnostic strategies are scarce and, in several cases, are not standardized and present low quality [11].

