### Target population and eligibility criteria

Children’s participation was voluntary. Our sample includes 3-to-10-year-old children seeking dental care at the Pediatric Dentistry clinic from our school, with at least one dental restoration in a primary tooth. The exclusion criteria were children whose parents did not consent to their participation, children who did not assent participating in this study, and children with limited ability to co-operate even when behavior management was used [18].

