**Table 1 Tab1:**
[figure not shown]
Clinical strategies for FDI and CARS criteria—adapted from Moro et al. [7]

^1^Based on Hickel et al. [16]

^2^Based on Pitts et al. [14]

Children will be followed for 24 months after the baseline interventions. Clinical assessments are being scheduled at 6-month intervals. In the baseline and at each follow-up visit, children are being instructed about diet and oral hygiene. The same examiner responsible for baseline evaluation will reassess the restorations at each appointment and propose a new treatment plan for each child based on the randomized strategy.

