## Discussion

The results from this study will provide necessary evidence regarding the economic impact of the possible implementation of potentially less interventionist diagnostic strategies, such as that based on CARS, when managing restorations in primary teeth. Owing to the lack of high-quality economic evaluation studies in the pediatric dentistry field [11], our study will strengthen the evidence and guide an evidence-informed decision-making process concerning diagnosing dental caries adjacent to restorations in primary teeth. To the best of our knowledge, no study has evaluated the economic impact of diagnostic strategies focused on such a clinical condition.

The strategy based on FDI may lead to a greater number of operative interventions [8], probably due to merge the assessment of the presence of recurrent caries and the restoration staining and adaptation. At first glance, the need for more interventions in the first treatment plan may lead to additional costs since the baseline. However, in a complete economic evaluation, not only costs are considered. Health outcomes are also important in determining the cost-effectiveness of a strategy [35]. Assuming a longer time horizon, we can expect as more interventionist; more reinterventions may be needed, as demonstrated in a previous clinical trial from our group [36]. Then, much higher expenses could have resulted. On the other hand, eventually, depending on how the non-intervened restorations behave during the follow-up, a different scenario may be observed, impacting on effects or not. Since it is an ongoing trial, the long-term health effects (at 2 years) will be crucial to decide, for assessment and management of restorations in primary teeth, whether a minimally invasive strategy (as that based on CARS) will be more efficient in allocating resources than the conventional one (based on FDI criteria).

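### The lifetime Markov model holds 24-month transition probabilities constant in every cycle, and no named sensitivity analysis relaxes this

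*Protocol article*

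**What the plan says.** Under Modelling for primary tooth lifetime horizon, the protocol article gives the source of the inputs: "Probabilities and costs will be extracted from the main trial". Literature values are added only if needed. It then fixes their course over time: "We will assume that probabilities will maintain the same at each cycle during the time horizon". The length of the model comes from a single typical child: "based on the mean age of children enrolled on the main trial, we will establish the number of cycles of the Markov model". The same section carries the deterministic and probabilistic strategies of the trial-based analysis over to the model.

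Those strategies are in Analytical methods. The one-way analysis gives costs, discount rate and effects as examples of what will be varied, and adds baseline conditions as covariates. The probabilistic analysis covers the same parameters. Constancy of the probabilities over cycles is not among them.

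On the data side, "Children will be followed for 24 months after the baseline interventions" (Comparators—interventions and follow-up, after Table 1), with assessments every 6 months. Time to new operative intervention is a secondary health effect, and a Cox model with shared frailty is planned for the need for a new intervention. On age: "Our sample includes 3-to-10-year-old children seeking dental care" (Target population and eligibility criteria).

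**The concern.** Building the lifetime model is the second stated aim of the plan (end of Background), and the Discussion counts on it to reduce the limits of extrapolating from one trial. What it adds to the 24-month result is the course after month 24. For that period the plan makes one assumption, gives no reason for it and names no alternative. The discount rate, by contrast, is explicitly tested from 0 to 10%.

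The two strategies could plausibly differ in how risk develops. The Background reports that under FDI "the indication of replacements of restorations in the baseline was more frequent than using the strategy based on CARS". The arms therefore leave baseline with different mixes of newly replaced and untouched restorations, whose risks need not follow the same course. If the hazard falls in one arm and rises in the other, equal per-cycle probabilities misstate the later cycles in opposite directions.

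The probabilistic analysis would not reveal this. Drawing different values for a probability changes its level, not its pattern over cycles. At stake is whether the lifetime acceptability curves look more certain than 24 months of data can justify.

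**Working it through.** **Plan's own figures.** There are none to reproduce. The article gives no transition probability, mean age, cycle length or number of cycles. Everything numerical below is an assumption chosen to show what the constancy assumption can do. The quantity is the cumulative risk of a first re-intervention, not the full model output.

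**Inputs (assumed).** The 24-month risk F is 30% for FDI and 20% for CARS. The horizon is 6 years, with 4.5 years as a check. Weibull shape k is 0.7 (falling hazard), 1 (constant) or 1.5 (rising hazard).

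**Formula.** The cumulative hazard at 2 years is H = −ln(1 − F), which is 0.3567 for 30% and 0.2231 for 20%. Risk at T years is 1 − exp(−H × (T/2)^k). At 6 years, (T/2)^k = 3^k, which is 2.158, 3 and 5.196 for the three shapes. Every shape reproduces the same 24-month risk.

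| Shape at 6 years | FDI | CARS | FDI − CARS (points) |
|---|---|---|---|
| Constant in both (k = 1) | 65.7% | 48.8% | 16.9 |
| 0.7 in both | 53.7% | 38.2% | 15.5 |
| 1.5 in both | 84.3% | 68.6% | 15.7 |
| 0.7 in FDI, 1.5 in CARS | 53.7% | 68.6% | about −15 |

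A common shape moves the absolute risks a great deal but hardly moves the contrast. Arm-specific shapes can reverse it. At 4.5 years the constant case gives 55.2% versus 39.5%, and the arm-specific case 46.7% versus 52.9%.

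**Arm difference ending at month 24.** Let CARS take the FDI constant hazard after 2 years. At 6 years FDI is 1 − 0.7³ = 65.7% and CARS is 1 − 0.8 × 0.7² = 60.8%. The difference is 4.9 points instead of 16.9.

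**Would the trial show it?** The probability in a 6-month interval is 1 − S(t + 0.5)/S(t), with S(t) = exp(−H × (t/2)^k). Over the four intervals:

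- FDI, k = 0.7: 0.126, 0.081, 0.070, 0.063, against 0.085 throughout if constant.
- CARS, k = 1.5: 0.028, 0.050, 0.064, 0.075, against 0.054 throughout if constant.

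Patterns of this size are worth looking for within 24 months.

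**Mean age.** Assume ages uniform from 3 to 10 (mean 6.5), exfoliation at 11 and F = 30%, so the yearly hazard is h = 0.3567/2 = 0.1783. At the mean age, 4.5 years remain and the risk is 1 − exp(−4.5h) = 55.2%. Averaged over remaining lives of 1 to 8 years it is 1 − [exp(−h) − exp(−8h)]/(7h) = 52.2%. The shift is 3 points.

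**The case against.** **Fixed transitions are not a constant overall event rate.** The standard gamble values several tooth states. If the Markov model uses such states and the arms start with different mixes, the aggregate rate can change over cycles even with fixed transitions. A reader might infer that the plan carries the early arm difference unchanged to exfoliation and so settles the answer in advance. The documents do not support that, and the model structure is in Supplemental File 3, which is not shown. What stands is that each transition probability is stated, without exception, to be the same in every cycle.

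**The Discussion does not predict late catch-up.** It says that "depending on how the non-intervened restorations behave during the follow-up, a different scenario may be observed". A reader might take this as a forecast of reversal after month 24, but it concerns the follow-up period, which the trial observes. Likewise, the primary effect counts interventions after the baseline assessment. FDI's extra baseline replacements are therefore a starting state and do not prove that the later hazard varies.

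**The contrast may be robust.** This stands for any shape common to both arms, as the working shows. Only arm-specific shapes, or a difference that fades, change the contrast materially.

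**The sensitivity list is open.** It is worded as examples, so more could be added. But nothing named there relaxes constancy, and varying the value of an effect is not the same as varying its time course.

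**Age is partly handled.** Age subgroups (3 to 6 versus 7 to 10 years) are planned, and a mean-age base case is ordinary for a cohort model. This stands, and age is a minor part of the point. A reader might also infer that the trial can supply age-dependent exfoliation, but the article does not say that exfoliation dates are recorded, nor does it make exfoliation a constant-probability transition.

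**Conclusion.** The point holds as a cheap improvement to a secondary analysis. The plan fixes constant probabilities over the primary molar lifetime from 24 months of data and names no analysis that relaxes this. Uncertainty about persistence of the arm difference after month 24 is thus missing from the lifetime results.

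The possible size runs from negligible to a reversal. Under assumed 24-month risks of 30% and 20%, the 6-year difference is 15.5 to 16.9 points in favour of CARS with a common shape, 4.9 points if the difference ends at month 24, and about 15 points in favour of FDI with shapes 0.7 and 1.5. The risks, shapes and horizon are all assumed, so this shows what can happen, not what is likely. The starting-age component is about 3 points on average under assumed exfoliation at age 11.

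Two limits apply. The 24-month primary evaluation is unaffected. And the trial's data cannot establish the hazard shape beyond 24 months, so a check within follow-up informs the later shape but does not settle it. The later shape has to be handled as scenarios.

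**What to change.** Before the economic analysis starts, add to the modelling section:

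1. Use the 6-monthly tooth-level data to check, by arm, whether re-intervention probabilities are constant over the four intervals. Use time-dependent probabilities where the data support them, and otherwise keep constant probabilities as the base case.
2. In either case, pre-specify three scenarios: (a) arm-specific time-varying probabilities; (b) the arm difference ending at month 24; (c) starting ages across 3 to 10 years, as a minor addition.
3. State that the shape after month 24 is a scenario assumption, and report the lifetime results under each scenario.

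The cost is a little more modelling work, with no new data collection. Later-cycle estimates will be less precise and the lifetime uncertainty wider. The article reports that the economic evaluation had not begun, so the change can still be made in advance.

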## Discussion

The results from this study will provide necessary evidence regarding the economic impact of the possible implementation of potentially less interventionist diagnostic strategies, such as that based on CARS, when managing restorations in primary teeth. Owing to the lack of high-quality economic evaluation studies in the pediatric dentistry field [11], our study will strengthen the evidence and guide an evidence-informed decision-making process concerning diagnosing dental caries adjacent to restorations in primary teeth. To the best of our knowledge, no study has evaluated the economic impact of diagnostic strategies focused on such a clinical condition.

The strategy based on FDI may lead to a greater number of operative interventions [8], probably due to merge the assessment of the presence of recurrent caries and the restoration staining and adaptation. At first glance, the need for more interventions in the first treatment plan may lead to additional costs since the baseline. However, in a complete economic evaluation, not only costs are considered. Health outcomes are also important in determining the cost-effectiveness of a strategy [35]. Assuming a longer time horizon, we can expect as more interventionist; more reinterventions may be needed, as demonstrated in a previous clinical trial from our group [36]. Then, much higher expenses could have resulted. On the other hand, eventually, depending on how the non-intervened restorations behave during the follow-up, a different scenario may be observed, impacting on effects or not. Since it is an ongoing trial, the long-term health effects (at 2 years) will be crucial to decide, for assessment and management of restorations in primary teeth, whether a minimally invasive strategy (as that based on CARS) will be more efficient in allocating resources than the conventional one (based on FDI criteria).

CEA is one of the most widely used economic evaluations in healthcare, as the effects are clinical measures [35, 37]. We opted to use different parallel economic evaluations at this protocol to bring different perspectives and additional subsidies to decision-makers. In this sense, we considered the primary health effect as the number of new operative interventions. This outcome represents the effect magnitude explored when comparing the diagnostic strategies in the trial. Although other endpoints (effects) have been set as secondary ones, they may show additional views to decision-makers. They offer perspectives regarding the time to the effect, demand for treatment, and patient-centered opinions that may also be helpful when implementing one or another in the health system.

On the other hand, patients/parents preferences and consequent utility values may also influence the final impression about the economic aspects of implementing the minimally invasive strategy, like CARS, in clinical practice. In this sense, CUA would be a valuable tool since it integrates patient-centered care philosophy and should be used when the quality of life is an important outcome [27]. CUA evaluates the effects on qualitative and quantitative health gains, often measured through QALYs. These are the product of time and utility obtained through the patient’s preferences for different health states [27]. As dental caries in children has a relevant impact on quality of life [38], studies involving the economic implications of caries diagnosis and management would benefit from CUA.

Utilities related to health states related to dental caries in primary teeth have been assessed through pre-scored multi-attribute health status classification systems, such as the CHU-9D, or through the visual analog scale (VAS) [39, 40]. One of the main concerns about pre-scored measures is that they may not identify the impact of oral diseases, such as dental caries [41]. Besides, the scaling methods will not necessarily express participants’ sacrifice is willing to take to achieve the health states, and they are more prone to contextual bias [42]. Conversely, the SG is a choice-based method of obtaining “patients” preferences for health states under uncertainty. Although it is time-consuming, the SG is conceptually based on the expected utility theory [43], and it involves the highest sacrifice the participants are willing to take. Finally, in this SG experiment, we could anchor the utility weights in tooth loss, considering it is our worst scenario planned and called the measure derived from it as tooth-related QALY. Although its questionable interchangeability to general QALYs, tooth-related QALY may be a relevant measure for decision-makers in dentistry, especially considering primary teeth, the type of injuries, and their health consequences in children.

Given the SG experiment inherent complexity, we decided to adopt the parents’ valuation of utility as a proxy measurement from the child’s preferences related to their oral health states. This approach has been widely used in studies of children’s preferences [44]. Although these proxy answers have some limitations, it would be a reasonable and feasible approach to a first attempt in determining utility scores related to dental caries, independently of the child’s age. Due to the broader age range in the base clinical trial, we opted for this approach.

Therefore, the results of these trial-based economic evaluations may bring actual evidence about the economic impact of such implementation and contribute to the decision-making process pertaining to the assessment and management of restorations in children. Analytical strategies adopted (e.g., probabilistic sensitivity analyses (scenario) and modelling for primary molars lifespan) may be alternatives to minimize possible limitations in results extrapolation derived from single-studies economic evaluations [45]. In this sense, they may permit that the results are broadly generalized to children seeking dental treatment, who will demand decision and management of their previously placed restorations.

## Trial status

CARDEC-03 trial recruitment took place from November 2017 to November 2018. Each patient will be followed for 24 months. Due to the COVID-19 pandemic situation, our goal is to complete the follow-up by May 2021.

## Data Availability

Data sharing does not apply to this article as no datasets were generated or analyzed during the current study.

## Abbreviations

FDI: World Dental Federation
CARS: Caries around restorations and sealants
CEA: Cost-effectiveness analysis
ECOHIS: Early Childhood Oral Health Impact Scale
CUA: Cost-utility analysis
QALYs: Quality-adjusted life years
ICER: Incremental cost-effectiveness ratio
ICCMS: International Caries Classification and Management System
ICDAS: International Caries Detection and Assessment System
HEAP: Health Economic Analysis Plan
RCT: Randomized controlled trial
ISPOR: International Society for Pharmacoeconomics and Outcomes Research
CARDEC: Caries detection in children
OHRQoL: Oral health-related quality of life
SG: Standard gamble
